		**Outcome based these assumptions**	
			The minimum sample size for model development is 1,204 observations.
**Feasibility**	The TriNetX sample, derived from the pilot study, captures approximately 14,234 people with epilepsy prescribed valproate between 2015–2018, with around a third subsequently withdrawn. This is sufficient. We have also undertaken a CPRD feasibility search, identifying 29,332 men and 15,315 women with epilepsy prescribed valproate in between 2010–2021, which should also generate sufficient numbers.		

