We recently published a study of 8,991 men and 5,243 women aged 16–54 with epilepsy taking valproate in TriNetX [20]. This was a survival analysis assessing 5-year mortality and morbidity in those withdrawn from valproate between 01/06/2015–01/06/2018 (regardless of whether switched to another ASM), with propensity-matched comparisons to those who remained on valproate. Results suggested substantially increased risks of emergency department (ED) attendances, hospital admissions, falls, injuries, burns and new-onset depression in both men and women withdrawn from valproate [20]. However, these were aggregate data designed to scope potential trends and generate hypotheses, not to probe causal links.

To progress the field, we propose a comprehensive study examining mortality and morbidity outcomes in individuals who either continued valproate, switched to lamotrigine or levetiracetam, or discontinued valproate. Employing a novel approach known as target trial emulation [21,22], this study will replicate a hypothetical randomised-controlled trial (RCT) using person-level retrospective observational data from both TriNetX and Clinical Practice Research Datalink (CPRD, which encompasses 60m UK patients) [23]. Target trial emulation minimises confounder and selection biases in observational studies by statistically emulating randomisation at baseline (time 0) [21]. Individuals are then analysed based on the treatment strategy aligned with their data. Results are available quickly and shown to mirror those of an RCT [21]. This offers a cost-effective and immediate alternative to conducting an RCT [21]; crucial given the urgency for information on valproate withdrawal safety amidst ongoing regulatory changes [24,25]. Additionally, the emulation facilitates creation of causal prediction models [26]. These are developed using observed data alongside causal theory and assumptions to calculate predicted risk under different hypothetical treatment conditions, allowing “what if” questions to be addressed for each potential (counterfactual) outcome [26]. This facilitates actionable prevention [26].

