### Hypotheses

Some morbidity or mortality outcomes will be increased when valproate is withdrawn, regardless of whether switched to lamotrigine, levetiracetam, or no new ASM;The causal prediction model developed will be able to predict which alternative ASMs are safest.

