#### Target trial emulation using observational data from TriNetX and CPRD

*Eligibility criteria*. Anonymised, person-level, electronic health data will be extracted from TriNetX and CPRD, linked across primary care, ED, inpatients, outpatients, and mortality subsets. The study period will be from 01/01/2014 to 01/01/2024. Included will be men and women aged 16–54 years. The study will take an open cohort design with patients entering the cohort when the following criteria are met:

Either: ≥1 epilepsy disease or symptom code recorded during the study period and two separate valproate prescription instances over the preceding 12 months before at least one of the epilepsy disease or symptom codes;

Or: ≥1 epilepsy disease or symptom code recorded any time before the study period with at least two separate valproate prescription instances over 12 months during the study period.

TriNetX and CPRD use ICD-10-CM and SNOMED codes, respectively. The coding strategy combining disease and symptom codes with valproate, as used our published study successfully [20], was shown to accurately identify epilepsy cases in our prior work [28,29].

Treatment arms:

Withdrawn valproate and commenced lamotrigineWithdrawn valproate and commenced levetiracetamWithdrawn valproate and no new ASM commencedContinues valproate

*Treatment assignment*. Baseline (time 0) will be defined as when valproate dose reduction commences (treatment arms 1–3) or prescription of valproate at a matched time (arm 4). Eligible individuals are assigned at baseline to the treatment strategy that their data are consistent with [21]. To emulate randomisation, adjustment is made for baseline confounders using Robins’ generalised methods (g-methods, e.g., inverse probability weighting) [21], considering age, sex, ethnicity, deprivation, type of epilepsy (using G40 codes), baseline seizure frequency (symptom codes recorded over preceding 12 months), alcohol excess, developmental delay, Cambridge Multimorbidity Score, length of valproate treatment, valproate dose, and ASMs used other than valproate. The final set of covariates required to adjust for confounding will be chosen using a causal directed acyclic graph [21].

*Outcomes*. These are listed in the target trial design section and derived from our prior work [1,20,30,31], and public consultation. All coded events will be recorded for flexible categorical or continuous analyses, as needed.

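### The TriNetX part of Aim 1 is not independent confirmation of Hypothesis 1, because the new TriNetX cohort contains the window of the pilot that helped suggest it

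*Protocol article*

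**What the plan says.** The Introduction describes the pilot: "We recently published a study of 8,991 men and 5,243 women aged 16–54 with epilepsy taking valproate in TriNetX". It assessed "5-year mortality and morbidity in those withdrawn from valproate between 01/06/2015–01/06/2018", whether or not another drug was started, against matched patients who stayed on valproate. It reports: "Results suggested substantially increased risks of emergency department (ED) attendances, hospital admissions, falls, injuries, burns and new-onset depression". Of its purpose, the protocol says "these were aggregate data designed to scope potential trends and generate hypotheses, not to probe causal links".

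Hypothesis 1 then reads: "Some morbidity or mortality outcomes will be increased when valproate is withdrawn". It names no outcome.

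The section on emulation using TriNetX and CPRD fixes the new data source: "Anonymised, person-level, electronic health data will be extracted from TriNetX and CPRD". It adds "The study period will be from 01/01/2014 to 01/01/2024", keeps the 16–54 age range, and reuses the pilot's coding strategy. Outcomes are taken from four earlier works, one of them the pilot, and from public consultation. The feasibility row of Table 1 says: "The TriNetX sample, derived from the pilot study, captures approximately 14,234 people with epilepsy prescribed valproate".

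The Contingency planning section offers cross-validation of findings between the two databases. It also lets either one serve as the fallback cohort if the other runs into limitations. No section excludes the pilot patients, holds data out, or names one database as the test of Hypothesis 1.

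**The concern.** A hypothesis suggested by one set of records is not tested independently by those same records. Where the new TriNetX cohort includes the pilot's patients and events, any chance excess, residual confounding or coding artefact in the pilot is present again in the new estimate. Because Hypothesis 1 names no outcome, the return of any one pilot signal would satisfy it.

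The consequence is practical. The Pathways to impact section plans to offer Aim 1 figures to the national valproate decision support tool and to share results with regulators. Readers could take a positive TriNetX result as a second, independent finding after the pilot. Under the contingency clause, TriNetX alone could end up carrying Hypothesis 1.

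**Working it through.** **The plan's own figure.** The 5% level appears only in the sample size code of Table 1. With p1 = 2977/8021 = 0.3712, p2 = 2471/8021 = 0.3081, two-sided 0.05 and power 0.80, its formula gives 880.73, rounded up to the stated 881. The arithmetic is right. The formula takes the test data as new.

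**Does the new cohort contain the pilot's window?**
- Pilot withdrawals: 01/06/2015 to 01/06/2018. Five years after the last is 01/06/2023.
- Study period: 01/01/2014 to 01/01/2024. Both the withdrawal window and the follow-up lie inside it.
- Age range and coding strategy are the same.
- 8,991 + 5,243 = 14,234, so the feasibility count is the pilot cohort itself.

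**How large is the overlap?** The documents give no fraction. If withdrawals were spread evenly over the study period (assumption), it is 3 years / 10 years = 30%. I also show 10%.

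**Pooled contrast.** If the pilot is a fraction f of the new sample, the correlation of the two test statistics is √f.
- f = 0.30: √0.30 = 0.548
- f = 0.10: √0.10 = 0.316

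**One arm.** Take each of arms 1–3 as one third of the withdrawn patients (assumption), with C continuers per withdrawn patient and the pilot a fraction f of both groups. In units of outcome variance over the number withdrawn:
- variance of the pilot contrast = (1 + 1/C)/f
- variance of the arm contrast = 3 + 1/C
- covariance = 1 + 1/C
- correlation = √[f(1 + 1/C)/(3 + 1/C)]

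With equal groups (C = 1) this is √(f/2). With about a third withdrawn, as Table 1 says (C = 2), it is √(0.4286 f).

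**Chance of repeating a false signal.** From the bivariate normal with no true effect, P(Z_new > 1.96 | Z_pilot > 1.96):

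| Overlap f | Contrast | Correlation | Probability |
|---|---|---|---|
| 0 | any | 0 | 2.5% |
| 0.10 | pooled | 0.316 | 10.1% |
| 0.10 | one arm, C = 1 | 0.224 | 7.1% |
| 0.10 | one arm, C = 2 | 0.207 | 6.6% |
| 0.30 | pooled | 0.548 | 21.4% |
| 0.30 | one arm, C = 1 | 0.387 | 12.9% |
| 0.30 | one arm, C = 2 | 0.359 | 11.7% |

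**Is chance the issue for emergency department attendance?** Mean proportion = 5448/16042 = 0.3396. Standard error = √(2 × 0.3396 × 0.6604 / 8021) = 0.00748. Then z = 0.06308/0.00748 = 8.4. Chance does not explain a signal of that size. What can recur is bias common to both analyses.

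**The case against.** A reader might infer that the new TriNetX sample is largely the pilot sample. The documents do not show this. Entry is open, the period is ten years against the pilot's three, and Table 1 gives a feasibility count, not the cohort definition. An overlap of 60% follows only if time zeros are limited to those able to reach five years by 01/01/2024 (3 of 5 years), and the plan sets no such limit. The pilot counts are themselves unsettled: 14,234 in the Introduction and feasibility row, but 2 × 8,021 = 16,042 in the calculations of Table 1.

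The new analysis also differs from the pilot. It uses person-level data, g-methods, four arms and recurrent-event models, where the pilot pooled all withdrawals. This is why the per-arm figures are the more relevant ones. The g-methods may reduce measured confounding, but they do not turn the same events into new evidence or remove unmeasured confounding.

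The hypothesis does not rest on the pilot alone. The Introduction cites valproate's efficacy and relapse in earlier studies, and several listed outcomes, such as death and aspiration pneumonia, are not among the pilot's reported increases.

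A reader might also take the Contingency planning section to claim that TriNetX replicates the pilot. It does not: it claims validation between TriNetX and CPRD, and this point does not dispute that.

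The pilot's role is openly disclosed, and moving from a scoping study to a causal analysis in the same database is legitimate. These objections limit the size of the problem. They leave in place the shared window, the lack of any separation of pilot patients and the missing designation of CPRD.

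**Conclusion.** The point holds in a limited form. Hypothesis 1 was suggested at least in part by TriNetX data, and the TriNetX arm of Aim 1 covers the same withdrawal window and follow-up. Its result is therefore not independent confirmation.

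The inflation above is conditional on an outcome having no true effect and having crossed 1.96 in the pilot. It also rests on the assumed overlap, equal arms, and a pilot nested in the new sample. Even at 10% overlap the probability is about 7% to 10%, well above 2.5%. For emergency department attendance the concern is carried-over confounding and coding bias; the documents give no test statistics for the other pilot outcomes. The CPRD test is not affected by this reuse. Should-fix: it changes what may be concluded from TriNetX and leaves the design intact.

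**What to change.** 1. In the Hypotheses and Contingency planning sections, name CPRD as the independent test of Hypothesis 1. State that TriNetX, if it becomes the sole cohort, cannot confirm that hypothesis.
2. Describe the TriNetX Aim 1 estimates as partly a re-analysis of hypothesis-generating data.
3. Add one TriNetX sensitivity analysis that excludes patients who met the pilot criteria, if those criteria can identify them. Dropping only time zeros within 01/06/2015–01/06/2018 is not enough: a pilot continuer who withdrew later can re-enter arms 1–3 with events already counted in pilot follow-up. If only time zeros can be dropped, report the analysis as reducing the overlap, not as confirmation.

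The cost is some wording and one extra analysis. TriNetX loses confirmatory standing for Aim 1, and the restricted analysis will be smaller with shorter follow-up. The full TriNetX sample stays in use for estimation and for Aim 2. The feasibility search found 29,332 + 15,315 = 44,647 people in CPRD over 2010–2021, so an independent dataset is already planned and lacks only the designation.

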### Contingency planning

Studying both TriNetX and CPRD allows external cross-validation of findings between the two databases, enhancing generalisability whilst providing a contingency study cohort should one dataset encounter limitations.

### Pathways to impact

The study will be published open-access in peer-reviewed journals and shared with regulators, charities, and PWE. Following our guide [34], we will explore various presentation formats for the externally validated prediction model including points-based systems, graphical score charts, and nomograms, as informed by PWE at public engagement workshops and clinicians at scientific conferences. An interactive version of the final causal prediction model will be deposited online in a public repository (as was did for the mortality prediction tool we developed previously: https://seds-tool.github.io/seds), making it globally accessible. We did similar with the CHA₂DS₂-VASc score we created and deposited on MDCalc.com (www.t.ly/poRmb): now the most widely incorporated prediction tool for stroke prevention in atrial fibrillation globally, embedded in NICE guidelines (www.t.ly/d0d3W). We will also add the model to the Civic Data Cooperative (https://civicdatacooperative.com/about) Digital Commons (https://github.com/civicdatacoop) to facilitate integration into health system core infrastructure.

Colleagues at our centre who created NHS England’s valproate decision support tool (www.t.ly/NFi5m) are in support of figures generated in addressing Aim 1 being added to the medication change “risks to you” section on page 4, alongside including a link to the online version of the causal prediction model generated in addressing Aim 2 [10].

### Ethics and dissemination

The University of Liverpool Research Ethics Committee has provided formal ethics review exemption for this study as it does not involve human participants, human tissue or personal data (REC Ref. 14455). Dissemination is outlined in the pathways to impact section.

### Data management plan

Data will be curated through University of Liverpool’s (UoL) Active Data Storage -a centralised, secure, supported data storage facility with multiple layers of protection. Data are replicated between two secure physical locations and backed up regularly. A regular tape backup is made to a third physical location, and segregated from the public network both physically and logically. Data are encrypted in transit using SSL.

We will use a public repository (www.github.com) to make all diagnostic and outcome coding algorithms, metadata, and R analysis scripts used publicly available, facilitating external replication and adaptation.

All data storage and use will comply with legal obligations (including GDPR) and UoL’s Research Data Management Policy.

### Study status and timeline

Funding has been received from the Epilepsy Research Institute and the Academy of Medical Sciences to proceed with this study. Permissions to access study data are being sought and PhD students to help complete the study are being recruited. We plan to complete the study within 36 months of protocol submission/publication
